### **3.2. Sample size**

The sample size was calculated using PASS (Power Analysis and Sample Size), version 11 (Number Cruncher Statistical Systems). The calculation was based on detecting a MCID of 7 points on Oswestry Disability Index (ODI), with a standard deviation of 15.1 points derived from a pre-trial study. A statistical power of 90% and a two-sided alpha of 0.05 were assumed. The calculation was based on the primary objective of demonstrating the superiority of the combination therapy over YBT or LOPM alone, using the Dunnett's test for the two primary comparisons. The initial calculation indicated a requirement of 113 participants per group. After accounting for a 15% dropout rate, the sample size was set at 133 participants per group. To ensure robust multi-center recruitment, the target sample size was further increased to 146 participants per group.

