## 6.3. Disc resorption assessment

At the 26-week post-randomization follow-up, a repeat MRI will be performed. The change in the sagittal area of the disc herniation from baseline to 26 weeks will be measured, with a reduction of  $\geq 40\%$  defined as the occurrence of disc resorption. The disc resorption rates will be calculated.

The maximum area of each disc herniation was measured on sagittal T2-weighted MRI sequences using Image J software (National Institutes of Health, Bethesda, MD, USA), with tracings made from the posterior edge of adjacent vertebrae in accordance with the measurement standards and definitions established by the North American Spine Society (NASS), the American Society of Spine Radiology (ASSR), and the American Society of Neuroradiology (ASNR) task force. All measurements were independently performed by two spine surgeons with extensive experience, and the average of their measurements was taken as the final result. The reliability assessment demonstrated good to excellent reproducibility.

The following table summarizes the data collection schedule and key assessment time points:

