### **10.6 Statistical method**

The primary efficacy analysis will follow the intention-to-treat (ITT) principle, including all randomly assigned patients. All analyses will be performed using R software, version 4.4.0 (R Foundation for Statistical Computing). Missing data for the longitudinal outcomes will be handled under the assumption of missing at random using multiple imputation. Imputation will be performed using the Multivariate Imputation by Chained Equations (MICE) package in R, generating 5 imputed datasets. The imputation model will include all longitudinal outcome measures from all-time points and all baseline covariates listed above. Results from the imputed datasets will be pooled according to Rubin's rules. Baseline characteristics will be summarized using descriptive statistics. For the continuous outcomes, between-group differences at each specific time point and within-group changes from baseline will be evaluated via pairwise comparisons of the estimated marginal means derived from the linear mixed model (LMM), which will be fitted using the lme4 package (version 1.1.35). These comparisons will be conducted using the emmeans package (version 1.10.0) with Tukey's method for adjustment of P values to control the

family-wise error rate. The model will include fixed effects for treatment group, time (modeled as a categorical factor), and their interaction. The model will be adjusted for the following prespecified baseline covariates: sex, age, body mass index, total duration of lumbar disc disease, duration of the current progressive episode, and degree of herniation at the symptomatic disc level. For categorical outcomes, between-group comparisons will be performed using the chi-square test or Fisher's exact test as appropriate, while the Bonferroni correction will be applied to adjust the significance level and control for type I error arising from multiple comparisons. All statistical tests will be two-sided, with a P value of less than .05 considered statistically significant. Institute of Basic Research in Clinical Medicine, China Academy of Chinese Medical Sciences will perform all statistical analyses.

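### Minor improvement: in Protocol 10.6 a step-down procedure would give disc resorption more power than Bonferroni at the same family-wise error control

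*Protocol*

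**What the plan says.** Protocol section 10.6 sets the tests for categorical outcomes: "between-group comparisons will be performed using the chi-square test or Fisher's exact test as appropriate". It adds that "the Bonferroni correction will be applied to adjust the significance level and control for type I error arising from multiple comparisons". The number of comparisons in the family is not given, and no sequential procedure is named. The next sentence reads "All statistical tests will be two-sided, with a P value of less than .05 considered statistically significant".

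The outcomes concerned follow from sections 6.1 and 6.3. Disc resorption at week 26 (a reduction of at least 40% in sagittal herniation area on MRI) is a secondary outcome. Section 6.3 says only that "The disc resorption rates will be calculated", with no expected rate and no power statement. Adverse events are the other listed outcome that would be categorical.

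The primary outcome, change in ODI to week 2, is handled differently. Section 3.2 sizes the trial for "demonstrating the superiority of the combination therapy over YBT or LOPM alone" with Dunnett's test for two comparisons. Section 10.6 analyses continuous outcomes by mixed-model contrasts "with Tukey's method for adjustment of P values to control the" family-wise error rate.

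**The concern.** Single-step Bonferroni holds every comparison to the strictest level, even after another hypothesis in the family has been rejected. Holm relaxes the level after each rejection and keeps strong family-wise control under any dependence between the tests.

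Three arms allow more. If one of the three pairwise nulls is false, at most one other can be true, because two equalities imply the third. So once the smallest P value passes 0.05/3, each of the other two can be tested at 0.05 (Shaffer's modification).

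For resorption, the question that parallels the trial's objective is whether the combination exceeds each component. That needs two rejections, and the single-step rule costs most when several rejections are needed. What is at stake is a real resorption benefit over both components being reported as not significant because of the choice of correction.

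**Working it through.** **The plan's own figure.** The protocol gives a sample size only for ODI: "detecting a MCID of 7 points on Oswestry Disability Index", SD 15.1, and "A statistical power of 90% and a two-sided alpha of 0.05 were assumed". With the two-sided Dunnett critical value for two comparisons (2.212) and z = 1.282:

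n = 2 × (15.1 × (2.212 + 1.282) / 7)² ≈ 113.6, against the stated 113 per group.

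113 / 0.85 = 132.9, rounded up to 133, and 146 × 3 = 438. The figures reproduce. They concern ODI only; nothing comparable exists for resorption.

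**Inputs for resorption.**
- From the protocol: three arms, 1:1:1, 146 per arm; 15% dropout, giving 146 × 0.85 ≈ 124 scans per arm.
- Assumed, because the protocol gives none: resorption of 20% or 30% in each single-treatment arm, and 15 or 20 points more in the combination arm.

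**Rules compared**, using pooled chi-square tests.
- Three pairs: Bonferroni (0.0167 each); Holm (0.0167, 0.025, 0.05); Shaffer (0.0167, then 0.05 and 0.05).
- Two comparisons with the combination: Bonferroni (0.025 each); Holm (0.025, then 0.05).

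Every step-down threshold is at least as large as the Bonferroni one, so nothing Bonferroni rejects can be lost. This does not depend on the assumed rates.

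**Power (%) to show the combination exceeds both components**, by summing binomial probabilities over all outcomes. Simulation with 400,000 replicates per scenario agrees to about 0.2 points wherever both were run.

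| Single / combination | n per arm | Bonferroni, 3 | Holm, 3 | Shaffer, 3 | Bonferroni, 2 | Holm, 2 |
|---|---|---|---|---|---|---|
| 20 / 35 | 124 | 44.5 | 50.9 | 60.3 | 51.1 | 62.0 |
| 20 / 35 | 146 | 54.7 | 60.9 | 70.0 | 60.9 | 71.4 |
| 20 / 40 | 124 | 77.4 | 82.1 | 87.7 | 82.0 | 88.4 |
| 20 / 40 | 146 | 86.0 | 89.5 | 93.3 | 89.4 | 93.7 |
| 30 / 45 | 124 | 35.2 | 40.9 | 50.3 | 41.2 | 52.4 |
| 30 / 45 | 146 | 44.5 | 51.5 | 59.9 | 51.7 | 61.5 |
| 30 / 50 | 124 | 69.0 | 74.0 | 81.0 | 74.0 | 82.0 |
| 30 / 50 | 146 | 78.2 | 83.8 | 88.6 | 83.7 | 89.3 |

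**Gains over Bonferroni.** Holm over three pairs: 3.6 to 7.0 points. Shaffer: 7.3 to 15.8. Holm over two: 4.4 to 11.1. The smallest gains all come from 20 / 40 at n = 146, where Bonferroni already reaches 86%; in the other seven rows the gains are about 5-7, 10-16 and 5-11 points.

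**At least one rejection.** The first step is the same for all three-pair rules. For 20 / 35 at n = 146, power to reject at least one of the two combination comparisons is about 83% under each.

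**Family-wise error, three pairs.** With equal rates in all arms (20% or 30%), 0.043 to 0.044 under all three rules. With one arm different, the one true null is rejected with probability 0.028 to 0.043 under Holm and 0.046 to 0.052 under Shaffer. The slight excess over 0.05 belongs to the chi-square approximation of a single 0.05 test, not to the step-down rule.

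**The case against.** The strongest reply is that nothing here is wrong. Bonferroni is prespecified, controls the type I error, is simple, and has matching simultaneous intervals. For a secondary outcome with no power claim, preferring intervals to power is defensible. This stands: the point is an optional gain in efficiency.

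The level 0.0167 is an inference. Section 10.6 does not give the family size, and two comparisons at 0.025 are equally compatible with the text. With two, Shaffer's step does not apply and the relevant gain is Holm's 4-11 points. The family size may properly be left to a statistical analysis plan.

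A reader might infer more than the protocol supports:

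- **That 10.6 contradicts itself**, setting a Bonferroni level and then .05 for all tests, so that three unadjusted tests would run a family-wise error of about 12%. That figure arises only if the Bonferroni clause just before the .05 sentence is ignored. The ordinary reading is that .05 is the overall level to which the stated adjustments apply.
- **That the trial's main question loses power.** The superiority objective in 3.2 rests on ODI, sized with Dunnett and analysed with Tukey. Bonferroni does not touch it.
- **That other categorical efficacy outcomes are affected.** None is named.

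**Conclusion.** A cheap improvement of minor weight. Single-step Bonferroni for disc resorption is valid but less powerful than a step-down rule with the same family-wise error control. That ordering is a matter of logic and needs no assumed rates.

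The size does depend on assumptions: single-arm rates of 20-30%, a combination benefit of 15-20 points, and 124-146 scans per arm. Within that range, power to show superiority over both components rises by about 4-7 points (Holm, three pairs), 7-16 points (Shaffer, three pairs) or 4-11 points (Holm, two comparisons). On a wider grid, with single-arm rates of 10-40% and benefits of 10-20 points, the three-pair gains run from 1.4 to 7.0 points for Holm and from 2.5 to 16.7 for Shaffer.

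**What to change.** In section 10.6, replace the Bonferroni wording for disc resorption with:

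*P values for the pairwise comparisons of disc resorption will be adjusted by Holm's step-down method (with Shaffer's modification if all three pairs are tested: 0.0167, then 0.05 and 0.05; if only the two comparisons with the combination are tested: 0.025, then 0.05), and an adjusted P<.05 is significant.*

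Keep the branch that matches the intended family and strike the other, before treatment allocation is disclosed to the analysts. Leave the existing Bonferroni wording in force for adverse-event comparisons.

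The cost is one sentence and a few lines of code, with no extra patients or scans. For the three-pair version, the adjusted P values are 3p₁ for the smallest and max(3p₁, p) for each of the other two, capped at 1. The real downside is that step-down P values have no simple matching simultaneous confidence intervals; ordinary or Bonferroni intervals would be shown beside them and labelled as such.

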## **11. Ethical issues**

### **11.1. Ethic review**

This study will follow the Declaration of Helsinki and Chinese regulations for clinical trials. Before starting, the study protocol will be reviewed and approved by EC at each study site. The comments of EC may include agreement, agreement after necessary revision, disagreement, and termination or suspension of the approved study.

### **11.2. Ethical review system**

#### **(1) Ethical oversight structure**

##### **1) Lead EC**

① Role: Will review the scientific validity and ethical compliance of the study protocol.

② Output: Will issue approval documents disseminated to:

PIs at all participating sites, local ECs, and QC team.

##### **2) Local institutional ECs**

① Role: Will assess site-specific feasibility, including:

Investigator qualifications and facility/infrastructure adequacy.

② Output: Approval documents will be forwarded to: Lead PI, lead EC, and QC team.

##### **(2) Authority and limitations**

1) No protocol modifications: Local ECs cannot alter core elements (e.g., drug dosage, inclusion/exclusion criteria).

2) Study suspension power: Local ECs must halt trials if ethical violations are identified.

##### **(3) AE Governance**

1) SAE review: Local ECs must convene within 48 hours of SAE occurrence.

2) Cross-institution notification: Conclusions will be shared with lead EC and all participating site ECs.

##### **(4) Protocol amendments**

1) Initiation: Local ECs may request amendments only to enhance participant protection.

2) Process: Requires:

- ① Written justification;
- ② Lead EC approval;
- ③ Uniform implementation across all sites.

(5) Inter-EC communication

1) Mandatory channels: Secure email/encrypted platforms for:

- ① Expedited SAE reporting;
- ② Amendment requests.

2) Response time:  $\leq 72$  hours for critical issues.

### **11.3. Benefits and risks assessment**

#### **11.3.1 Potential benefits**

Participants may derive the following direct benefits from this study:

(1) Enhanced medical care:

- 1) Standardized diagnostic evaluations.
- 2) Protocol-defined therapeutic interventions.

(2) Clinical improvement:

Potential alleviation of LDHR symptoms (e.g., pain, mobility).

Note: Benefits are neither guaranteed nor the primary study objective.

#### **11.3.2 Anticipated risks**

(1) Treatment-related risks:

1) LOPM:

- ① Transient exacerbation of lumbar pain;
- ② Increased lower limb numbness/radicular pain.

2) Pharmacotherapy:

- ① Gastrointestinal events (e.g., nausea, constipation);
- ② Allergic dermatitis.

(2) Disease progression risks:

- 1) Failure to achieve symptom relief.
- 2) Rare but severe events (e.g., cauda equina syndrome).

#### **11.3.3 Risk mitigation strategies**

- (1) Pre-screening: Exclusion of high-risk participants (e.g., spinal instability).
- (2) Real-time monitoring: Protocol-defined thresholds for therapy discontinuation.
- (3) SAE protocols: Immediate surgical referral for neurological deficits.

## **11.4. Informed consent process**

### **11.4.1 Pre-enrollment requirements**

(1) Comprehensive disclosure:

1) Investigators must provide written and verbal explanations (in lay language) covering:

- ① Study purpose and duration;
- ② Potential benefits and risks;
- ③ Alternative treatment options.

2) Use approved consent documents (vetted by the EC).

(2) Participant rights:

- 1) Emphasize the right to withdraw at any time without penalty.
- 2) Clarify voluntary participation (no coercion).

(3) Documentation:

- 1) Signed informed consent forms must be obtained prior to any study procedures.
- 2) Store original informed consent forms in secure, access-controlled archives.

### **11.4.2 Special circumstances**

(1) Legally authorized representatives: Will be permitted for cognitively impaired participants.

(2) Re-consent: Will be required for substantial protocol amendments affecting risks/benefits.

## **11.5. Participant recruitment procedures**

### **11.5.1 Recruitment methods**

(1) On-Site advertising:

Posters will be displayed in clinics/hospitals of participating centers, including:

- 1) Study title/purpose.
- 2) Eligibility criteria (age, diagnosis, etc.).
- 3) Contact information.

(2) Digital outreach:

WeChat (and other approved social media platforms) will be used to disseminate:

- 1) EC-approved recruitment notices.
- 2) Pre-screening questionnaires (to assess preliminary eligibility).

### **11.5.2 Eligibility verification**

Two-stage screening:

(1) Initial screening: Will be conducted by research coordinators via phone/online forms.

(2) In-person confirmation: Full assessment against inclusion/exclusion criteria by investigators.

### **11.5.3 Ethical compliance**

- (1) Ad content review: All materials will be pre-approved by the EC to avoid undue influence.
- (2) No coercive language: Prohibited phrases (e.g., “Guaranteed cure”).

## **11.6. Participant rights and protections**

### **11.6.1 Voluntary participation & withdrawal rights**

- (1) Voluntary consent:

Participation is entirely voluntary, with no impact on:

- 1) Clinical care quality.
- 2) Patient-provider relationship.
- 3) Access to alternative treatments.

- (2) Unpenalized withdrawal:

- 1) Participants may withdraw at any time without justification.
- 2) Standard-of-care therapies will remain available.

### **11.6.2 Medical record handling**

- (1) Documentation standards:

- 1) All research data (e.g., CRFs, lab reports) will be integrated into hospital medical records.
- 2) Original research documents will be archived securely.

- (2) Access permissions:

- 1) Authorized access will be limited to:

- ① Study investigators;
- ② Regulatory inspectors;
- ③ ECs.

- 2) De-identification: Published data will exclude personally identifiable information.

### **11.6.3 Privacy safeguards**

- (1) Legal compliance: Will adherence to China’s Personal Information Protection Law.
- (2) Data anonymization: Research datasets will use unique participant codes.

## **11.7. EC continuing review**

### **11.7.1 Scope and frequency of review**

The EC must conduct continuing reviews of all approved studies at least annually, covering:

- (1) Protocol amendments:

- 1) Assess scientific/ethical validity of proposed changes (e.g., new risks, procedures).
- 2) Verify re-consent requirements for ongoing participants.

- (2) SAEs:

- 1) Review aggregated SAE reports to evaluate risk-benefit balance.
- 2) Require immediate ad-hoc reviews for unexpected fatal/life-threatening SAEs.

(3) Annual progress reports:

Evaluate:

- 1) Enrollment rates.
- 2) Withdrawal reasons.
- 3) Interim safety data.

### **11.7.2 Review procedures**

(1) Full-committee review for:

- 1) First renewal.
- 2) High-risk amendments (e.g., dose escalation).
- (2) Expedited review for minor changes (e.g., typographical corrections).
- (3) Documentation:

All reviews will generate dated approval certificates or modification requests.

### **11.7.3 Regulatory compliance**

- (1) Deadlines: Annual reviews must occur  $\pm 30$  days of approval anniversary.
- (2) Non-compliance: Studies will lapse if renewal is overdue by  $>60$  days.

## **11.8. EC inspection procedures**

### **11.8.1 Roles and responsibilities**

During regulatory inspections or audits of the EC, the following personnel must comply with institutional Standard Operating Procedures:

(1) EC office secretary:

1) Prepare documentation: Organize and provide:

- ① Approved study protocols and amendments;
  - ② Meeting minutes and voting records;
  - ③ SAE review reports;
  - ④ Continuing review files.
- 2) Coordinate logistics: Schedule interviews, arrange meeting spaces.

(2) EC members:

1) Participate in interviews: Explain deliberation processes for:

- ① Initial approvals;
- ② Risk-benefit assessments;
- ③ Controversial decisions.

2) Defend ethical oversight.

(3) EC chairperson:

Lead inspections: Present overall EC governance, including:

- 1) Conflict-of-interest management.
- 2) Training records of members.
- 3) Annual performance self-assessments.

### **11.8.2 Inspection readiness**

(1) Pre-inspection:

- 1) Conduct mock audits biannually using checklists.
- 2) Ensure 72-hour document retrieval capacity.

(2) During inspection:

Provide unedited, timestamped records (no post-hoc modifications).

(3) Post-inspection:

Submit corrective action plans within 15 working days for identified deficiencies.

## **12. Storage and archiving of research materials**

(1) Active study phase

1) Storage location: All source documents and data must be kept in a dedicated, access-controlled research office at each study site.

2) Custodian: Will be managed by the site research assistant under the PI's supervision.

3) Access restrictions:

- ① Only authorized personnel (e.g., investigators, monitors) may handle materials.
- ② No unauthorized disclosure or removal will be permitted without written approval from the lead study unit.

(2) Post-study archiving

1) Centralized transfer: Within 30 days of study completion, all materials must be:

- ① Cataloged (e.g., indexed by participant ID/visit date).
- ② Securely packaged;
- ③ Transferred to the lead institution's archive.

2) Retention requirements:

- ① Will be retained for  $\geq 5$  years post-study, or longer if required by local regulations.
- ② Electronic data will be archived in read-only formats (e.g., PDF) with encrypted backups.

(3) Confidentiality safeguards

1) Anonymization: All shared datasets must remove personally identifiable information.

2) Destruction protocol: Post-retention, materials will be:

- ① Shredded (paper);

② Digitally erased (electronic) with certification.

### 13. Clinical summary

After the completion of statistical analyses, the statistical unit will release the statistical report with a seal.

### 14.2 Allocation of enrolled patients

| Clinical Center                                                 | Number of Patients          |
|-----------------------------------------------------------------|-----------------------------|
| Wangjing Hospital, China Academy of Chinese Medical Sciences    | Total n = 42 (14 per group) |
| Affiliated Hospital of Changchun University of Chinese Medicine | Total n = 33 (11 per group) |
| Affiliated Hospital of Shaanxi University of Chinese Medicine   | Total n = 33 (11 per group) |
| Affiliated Hospital of Shandong First Medical University        | Total n = 33 (11 per group) |
| Dongzhimen Hospital, Beijing University of Chinese Medicine     | Total n = 33 (11 per group) |

**The National Key Research and Development Program of China, No. 2021YFC1712802**

|                                                                               |                             |
|-------------------------------------------------------------------------------|-----------------------------|
| First Teaching Hospital of Tianjin University of Traditional Chinese Medicine | Total n = 33 (11 per group) |
| Gansu Provincial Hospital of Traditional Chinese Medicine                     | Total n = 33 (11 per group) |
| Guangdong Provincial Hospital of Chinese Medicine                             | Total n = 33 (11 per group) |
| Liaoning University of Traditional Chinese Medicine                           | Total n = 33 (11 per group) |
| Luoyang Orthopedic-Traumatological Hospital of Henan Province                 | Total n = 33 (11 per group) |
| Nanfang Hospital, Southern Medical University                                 | Total n = 33 (11 per group) |
| Suzhou Hospital of Traditional Chinese Medicine                               | Total n = 33 (11 per group) |
| The First Hospital of Hunan University of Chinese Medicine                    | Total n = 33 (11 per group) |

